### Intervention

The study group is exposed to DHA at a dose of 1500 mg/day orally (preconditioning dose), starting 7 days before the beginning of the first chemotherapy cycle, and carvedilol in a dose of 12.5 mg every 12 h orally (preconditioning dose), starting 2 days before the chemotherapy cycle. The daily doses of the preconditioning regimen are delivered 7 days before the first cycle of chemotherapy in a single, weekly, red pillbox with separate compartments per day. On the day of chemotherapy, after the recovery of the red pillbox, the second weekly pillbox (green) with separate compartments per day is delivered. Both preconditioning doses will last up to 2 days after the initial cycle. From day 3 after the first chemotherapy cycle until the seventh day (green pillbox) the doses of DHA and carvedilol will be reduced to 500 mg per day and 6.25 mg every 12 h, respectively (maintenance doses). Seven days after the first chemotherapy cycle, the green pillbox is recovered and three transparent pillboxes with separate compartments per day are delivered with maintenance doses. At the end of the 3 weeks, the transparent pillboxes are recovered and three new white pillboxes are delivered with maintenance doses. This reception and delivery of new pillboxes every 3 weeks is replicated until the end of the intervention. The control arm group will likewise be exposed to double placebo. This timing follows the standard breast cancer adjuvant protocol used by the Chilean public health system, based on four anthracycline cycles each, separated by 21 days. The addition of trastuzumab or any other oncologic therapy during the standard adjuvant protocol will not modify the intervention. The pharmacological protocol will be discontinued in any patient who develops congestive heart failure or any other adverse acute cardiac effect reverting to standard care and will be unblinded. Other adverse events will be monitored and reported during the trial in each clinical evaluation by a team physician as well as in the usual oncological controls by physicians who are not part of the research team. Recommendations for Interventional Trials (SPIRIT) checklist for this protocol is also provided (Additional file 1). Generic carvedilol and its placebos were purchased specifically for this study. Natrol® DHA Super Strength and was supplied free of charge by Nutrimarket Chile, a company not participating in the study.

### Follow-up protocol

Patients participate actively in this study for 6 months, at which point the second CMR is performed. One year after the first cycle of chemotherapy, a final phone contact is to be carried out.

Follow up is performed and monitored by trained study personnel who interview the patients by phone or in person, including:
Clinical follow-up at 30, 90 and 180 daysGeneral laboratory analyses: blood cell count and full-biochemistry profile, including creatinine and electrolytes, 2 and 4 days after the initial chemotherapy cycleNT-ProBNP and hs-cTnT plasma levels (by ELISA) 2, 4 and 90 days after the first chemotherapy cycleOxidative stress parameters analysis at days 2, 4 and 90 after the first chemotherapy cycleResting electrocardiogram 2, 4 and 90 days after the first chemotherapy cycleTransthoracic echocardiogram at 90 and 180 days after the chemotherapy cycleCMR at 180 days after the initial chemotherapy cycleFinal phone contact 1 year after the first chemotherapy cycle

### Study objectives – primary and secondary endpoints

The trial includes four co-primary endpoints to assess the efficacy of the proposed strategy to inhibit or attenuate the subclinical manifestations of anthracycline-induced cardiotoxicity (AIC). The co-primary endpoints include two imaging variables, a serum biomarker and electrocardiographic variables. The first co-primary endpoint is changes in LVEF from baseline control to 180 days after the first chemotherapy cycle, determined by CMR. The second co-primary endpoint is the percentage of changes in global longitudinal strain (GLS) comparing baseline with 90 and 180 days after the first cycle, determined by two-dimensional ECHO. The third co-primary endpoint is the elevation in serum biomarkers, including NT-ProBNP between baseline and 48 h after the first chemotherapy cycle and/or elevations in levels of hs-cTnT at 2, 4 and 90 days. The fourth co-primary endpoint is the prolongation in the corrected QT interval, 48 h after the first chemotherapy cycle.

Additionally, three secondary endpoints were included to determine other imaging and clinical variables, as well as to evaluate systemic biomarkers of oxidative stress. The first secondary endpoint is the occurrence of major adverse cardiac events during follow-up such as: cardiac death, acute coronary syndrome, acute pulmonary edema, clinical manifestations of heart failure and life-threatening arrhythmias. The second secondary endpoint is changes in LVEF from baseline compared to 90 and 180 days after the first chemotherapy cycle, determined by two-dimensional ECHO. The third secondary endpoints are biomarkers of oxidative stress damage, as well as parameters of intracellular and extracellular antioxidant balance. In order to evaluate the oxidative stress damage, plasma lipoperoxidation levels (malondialdehyde levels) will be measured at 2, 4 and 180 days after the initial chemotherapy cycle. To evaluate antioxidant balance, the Erythrocyte Thiol Index (GSH/GSSG) will be determined at 2, 4 and 90 days after the first chemotherapy cycle. Given this is a pilot study, outcomes will include the total number of patients screened, those eligible, those providing informed consent and those completing the intervention treatment.

### Timeline for participants

Figure 1 represents the patient timeline. Outlined in Fig. 2 is the study schedule of enrollment and assessments (Standard Protocol Items: Recommendations for Interventional Trials (SPIRIT Figure).

**Fig. 1 Fig1:**
[figure not shown]
Timeline of the Carvedilol-DHA (CarDHA) trial. *hs-cTnT* high-sensitivity cardiac troponin T, *NT-ProBNP* NT-proB-type natriuretic peptide, *EKG* resting electrocardiogram, *ECHO* echocardiography, *CMR* cardiac magnetic resonance, *DHA* docosahexaenoic acid

**Fig. 2 Fig2:**
[figure not shown]
Standard Protocol Items: Recommendation for Interventional Trials (SPIRIT) Figure (required for study protocols). *CMR* cardiac magnetic resonance, *DHA* docosahexaenoic acid, *ECHO* echocardiography, *hs-cTnT* high-sensitivity cardiac troponin T, *NT-ProBNP* NT-proB-type natriuretic peptide, *EKG* resting electrocardiogram

### Sample size and data analysis

The sample size was estimated on the basis of results from our previous protocol (63), where the carvedilol-supplemented group showed a 51% reduction of differential LVEF (ΔLVEF) compared with the placebo group. ΔLVEF was determined between the last follow-up ECHO at approximately 1 year (10–12 months) with respect to baseline ECHO, both performed by two-dimensional evaluation. Assuming normal distribution and a common relative standard deviation of 48% (supplemented group), with 5% two-sided significance, a sample size of 32 will be required to provide 80% statistical power to detect a 12.5% ΔLVEF reduction assessed by CMR to provide greater precision.

Results will be analyzed according to intention-to-treat criteria, including all randomized patients who are able to initiate intervention, independent of treatment and follow-up period durations. Continuous variables will be expressed as means ± standard deviation or medians and interquartile ranges depending on their distribution. Distribution will be analyzed using the Kolmogorov-Smirnov test. Student’s *T* test and Pearson correlation analyses will be applied for normally distributed continuous variables. The Mann-Whitney *U* test and Spearman’s correlation will be used for non-normally distributed continuous variables. Categorical variables will be expressed as numbers and frequencies (%). Differences between the frequencies will be performed by the chi-square test or by Fisher’s exact test. Multiple linear regression analysis will be used to assess independent predictors of the absolute semiannual changes in ΔLVEF, to identify factors associated with ΔLVEF. The difference between the groups will be considered significant with a *p* value of < 0.05.

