Clinical evidence has reported DHA to be safe in metastatic breast cancer patients treated with doxorubicin [59]. Additionally, we performed a three-arm pilot protocol in patients with localized breast cancer, treated with adjuvant doxorubicin: one group with a DHA-enriched formula; another with carvedilol; and a double placebo group. Eleven patients were exposed to 2 g per day of EPA + DHA from 7 days before to 7 days after the initial chemotherapy cycle, without showing any side effects associated with the formula [60]. The DHA-enriched formula inhibited NT-proB-type natriuretic peptide (NT-ProBNP) plasmatic elevation after doxorubicin chemotherapy (48 h), suggesting a subclinical cardiotoxicity attenuation and showed a trend towards a lower LVEF decline at 10–12 months when compared to the placebo group. The lack of statistical significance was probably due to the small sample size and the limitations associated with echocardiographic sensitivity. The eleven patients exposed to 12.5 mg carvedilol every 12 h showed a significant reduction in LVEF drop at 10–12 months (51% less drop), compared to the placebo group. Unexpectedly, in this study arm, carvedilol did not impact the levels of NT-ProBNP. The study population was older and had at least one major cardiotoxicity risk factor.

In the present study, we hypothesized that breast cancer patients treated with anthracycline, preconditioned with DHA and carvedilol a week before the first chemotherapy cycle and for 90 days afterwards, will have less subclinical AIC, compared to comparable patients exposed to double placebo. We consider as subclinical AIC any manifestation of cardiac injury, such as: decrease of left ventricular function by a drop of LVEF by CMR, a decline in global longitudinal strain by two-dimensional ECHO, elevation of biomarkers or electrocardiographic alterations.

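### The 80% power stated for the 180-day CMR change in LVEF rests on a 10–12-month echocardiographic effect and SD, with no step that converts them

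*Protocol article*

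**What the plan says.** Protocol article, Sample size and data analysis: the calculation starts from a previous study in which "the carvedilol-supplemented group showed a 51% reduction of differential LVEF (ΔLVEF) compared with the placebo group". The paragraph then explains how that quantity was obtained: "ΔLVEF was determined between the last follow-up ECHO at approximately 1 year (10–12 months) with respect to baseline ECHO", both by two-dimensional imaging. It assumes a common relative SD of 48%, attributed to the supplemented group, and a two-sided 5% test. It concludes that 32 patients give 80% power for a 12.5% reduction in ΔLVEF measured by CMR, and names greater precision as the reason for CMR.

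Study objectives: "The first co-primary endpoint is changes in LVEF from baseline control to 180 days after the first chemotherapy cycle, determined by CMR". Under Follow-up protocol, CMR is repeated at 180 days and echocardiography at 90 and 180 days. The one-year contact is by telephone.

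The Background describes the source of the 51%: "The eleven patients exposed to 12.5 mg carvedilol every 12 h showed a significant reduction in LVEF drop at 10–12 months (51% less drop"), against placebo. It adds: "The study population was older and had at least one major cardiotoxicity risk factor". The eligibility criteria of the present trial do not require a risk factor.

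The Discussion concedes that 6 months is short. It defends the choice with a cited median of 3.5 months from the end of chemotherapy to cardiotoxicity, and concludes that a difference at 6 months would be hard to miss.

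**The concern.** A power statement applies to one endpoint at one time, with an effect and an SD expected for that endpoint. Here the borrowed effect belongs to another modality (echocardiography), a later time (10–12 months) and an older population selected for risk. The paragraph mentions the change to CMR but not the shorter horizon, and puts no number on either. If the separation between arms is still developing at day 180, the effect could be smaller than the one borrowed. A null result would then be read against an 80% that was never derived for that scan, and the Discussion would encourage that reading.

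**Working it through.** **Inputs.** From Sample size and data analysis: effect in the previous study 51%, stated target 12.5%, relative SD 48%, two-sided 5%, power 80%, total 32. Allocation is 1:1 (Enrollment and baseline phase assessments), so 16 per arm. Effects and SD are read on one scale, as a percentage of the placebo decline.

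**Step 1: the plan's own figure.** Normal approximation: n per arm = 2(1.960 + 0.842)² × (SD/effect)² = 15.70 × (SD/effect)². Power uses the noncentral t with 30 degrees of freedom and noncentrality d√(16/2).

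| Effect / SD | d | n per arm for 80% | Total | Power at 16 per arm |
|---|---|---|---|---|
| 12.5 / 48 (stated) | 0.26 | 15.70 × 14.75 = 231.5, so 232 | 464 | 11% |
| 51 / 48 (previous study) | 1.06 | 15.70 × 0.886 = 13.9, so 14 (t test: 15) | 28 (t test: 30) | 83% |

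The stated pair does not give 32. The 51%/48% pair comes within two patients by the t test. It would give exactly 32 if 28 were inflated for 10% dropout (28/0.90 = 31.1, so 32), but no dropout allowance is stated. Other readings of the 12.5% also fail:
- A one-sided test needs 366 in total.
- With 32 per arm, power is 18%.
- If 48% is relative to the supplemented group's own mean, the SD is 0.48 × 49 = 23.5% of the placebo decline, and 112 patients are needed.

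So the only traceable route to about 32 patients and 80% runs through the 10–12-month echocardiographic effect.

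**Step 2: what moving to day 180 could do.** Let f be the fraction of the 51% difference present at day 180, with the difference still expressed against the 10–12-month placebo decline. The SD at day 180 is not given, so three assumptions are shown, each with 16 per arm.

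| f | SD unchanged (d = 1.0625f) | SD falls with √f (d = 1.0625√f) | SD falls with f (d = 1.0625) |
|---|---|---|---|
| 1.00 | 83% | 83% | 83% |
| 0.75 | 59% | 71% | 83% |
| 0.50 | 31% | 54% | 83% |

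**Step 3: the same question without reference to f.** Power at 16 per arm over assumed 180-day effects and SDs:

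| Effect | SD 36 | SD 48 | SD 60 |
|---|---|---|---|
| 51 | 97% | 83% | 64% |
| 40 | 86% | 63% | 45% |
| 30 | 63% | 40% | 28% |
| 12.5 | 16% | 11% | 9% |

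**Step 4: the Discussion's argument for 6 months.** The Intervention section gives four anthracycline cycles 21 days apart, so the last is on day 3 × 21 = 63. Day 180 is 117 days later, or 117/30.4 = 3.8 months. The cited 3.5-month median runs from the end of chemotherapy, so the endpoint scan falls only just past it. Counting from day 84, the end of the fourth 21-day interval, gives 96/30.4 = 3.2 months, which is before the median. On the protocol's own figure, around half of the eventual cases would not yet have appeared at the scan. That does not support the claim that a difference would be hard to miss.

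**The case against.** The strongest reply has five parts.

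- **The target is nominally the right one.** The sentence about the one-year echocardiogram describes the previous study. The next sentence states the powered difference as one assessed by CMR, which the trial measures. This stands. A reader might infer that the trial is powered for an endpoint it never measures, or that ΔLVEF has two contradictory definitions. The text does not go that far: it discloses borrowed planning data and does not convert them. The regression's reference to half-yearly change, though awkward, fits a 180-day ΔLVEF.
- **The 51% is not carried over unchanged.** The stated target is 12.5%. This also stands, but it does not rescue the 80%, since 12.5% with a 48% SD gives 11%.
- **A loss of power is not inevitable.** The SD is given as relative. If effect and SD both scale with the decline, d stays at 1.06 and power at 83%. This stands, and it rules out quoting the fall to 31% as a result.
- **Case timing is not mean change.** The 3.5-month median concerns patients who developed cardiotoxicity, while the endpoint is mean LVEF change in all patients. It therefore cannot be turned into a fraction of the effect present at day 180. It tests only the Discussion's own argument.
- **The direction is open.** The 51% is for carvedilol alone; this trial adds DHA, and CMR may be more precise. Either could raise power. A lower-risk population could lower it, but the protocol's remark that higher-incidence populations benefit more does not show that a relative reduction would shrink.

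The authors also list the small sample and short follow-up as limitations. That admission does not correct the power statement.

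**Conclusion.** The point holds in a limited form. The 80% power is not established for the 180-day CMR change: its only traceable basis is a 10–12-month echocardiographic effect with an SD apparently from the same study, in an older, higher-risk population, with no conversion to day 180 or CMR. The target actually stated gives about 11%.

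The size and sign of the further change in power at 180 days cannot be determined from the protocol. Starting from 51%/48%, with half the difference present, power is 31% to 83% according to the SD assumption alone, before any gain from CMR or DHA. These figures assume 16 evaluable patients per arm, a two-sided 5% t test, and effect and SD on the scale of the placebo decline. The statement should be corrected, because a null result would be read against it. The failure of 12.5%/48% to give 32 is the larger numerical error in the same paragraph, but restoring the 51% would not settle this point.

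**What to change.** In Sample size and data analysis:
- Define the powered ΔLVEF as the CMR change from baseline to 180 days, as in Study objectives, and use that definition in the regression.
- Label the 51% as a 10–12-month echocardiographic result for carvedilol alone in an older population with risk factors, and state the source and scale of the 48%.
- Reconcile both with the 12.5% target, preferably by giving the expected difference and SD in LVEF points.
- Replace the single 80% with the power of 32 patients over a stated range of 180-day effects and SDs, as in the Step 3 table.

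In the Discussion, soften the claim about differences at 6 months, and say that day 180 is about 3.8 months after a day-63 last cycle.

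The cost is rewording one paragraph and one Discussion sentence, and the stated power becomes less favourable. No patients or visits are added. Trial status reports 30 patients enrolled by 26 October 2018, so the practical change is to the power claim and not to the sample size.

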**Methods/design:**

We designed a pilot, randomized controlled, two-arm clinical trial with 32 patients to evaluate the effects of non-hypoxic cardiac preconditioning (DHA) plus carvedilol on subclinical cardiotoxicity in breast cancer patients undergoing anthracycline treatment. The trial includes four co-primary endpoints: changes in left ventricular ejection fraction (LVEF) determined by cardiac magnetic resonance (CMR); changes in global longitudinal strain (GLS) determined by two-dimensional echocardiography (ECHO); elevation in serum biomarkers (hs-cTnT and NT-ProBNP); and one electrocardiographic variable (QTc interval). Secondary endpoints include other imaging, biomarkers and the occurrence of major adverse cardiac events during follow-up. The enrollment and follow-up for clinical outcomes is ongoing.

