### Enrollment and baseline phase assessments

Patients diagnosed with localized breast cancer at the clinical campus are contacted by the study staff. After an initial clinical evaluation and explanation of the study protocol, patients agreeing to participate sign the informed consent followed by undergoing a baseline analysis including clinical evaluation and baseline laboratory and cardiovascular imaging to determine study eligibility. Baseline analyses are performed at least 10 days before the initial chemotherapy cycle, consisting of: (1) general laboratory testing, including blood cell count, INR/TTPA, full-biochemistry profile including serum creatinine and electrolytes; (2) plasma levels of NT-ProBNP and high-sensitivity cardiac troponin T (hs-cTnT); (3) resting electrocardiogram; (4) transthoracic echocardiogram; and (5) cardiac magnetic resonance. Breast cancer patients meeting the inclusion criteria are randomly allocated at a 1:1 ratio to either the intervention (DHA and carvedilol) or the control (double-placebo) arms. Randomization will be computer generated with homogeneous blocks of four by a specialist who is not related to the research group. The same person also assigns treatment and prepares the respective pillboxes with ad-hoc labeling and perform monitoring adherence. Patients, study staff, other care providers and data analysts are blinded to group allocation. The acquisition of the echocardiographic images will be performed by the same operator and will be reviewed by two other independent operators.

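### The stated 80% power for a 12.5% ΔLVEF reduction with 32 patients does not follow from the stated 48% relative SD; the printed inputs give about 11% to 31%

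*Protocol article*

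**What the plan says.** The section Sample size and data analysis starts from the group's own earlier study, in which the carvedilol arm "showed a 51% reduction of differential LVEF (ΔLVEF) compared with the placebo group". It sets the assumptions as follows: "Assuming normal distribution and a common relative standard deviation of 48% (supplemented group), with 5% two-sided significance". It concludes that "a sample size of 32 will be required to provide 80% statistical power to detect a 12.5% ΔLVEF reduction assessed by CMR". The sentence closes by appealing to the better precision of CMR, but attaches no CMR standard deviation, correlation or other number to that appeal.

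The Abstract describes a "two-arm clinical trial with 32 patients", and the section on enrollment says that patients are "randomly allocated at a 1:1 ratio". So 32 is the total, with 16 per arm. The change in LVEF by CMR from baseline to 180 days is the first co-primary endpoint and the only one with a power statement.

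**The concern.** The effect to be detected (12.5%) is about a quarter of the SD it is set against (48%). A two-arm comparison with 16 per arm normally needs a difference of about one full SD for 80% power, so the sentence looks wrong before any calculation.

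At stake is how the first co-primary result will be read. If the statement stands, a non-significant CMR result will look like reasonably powered evidence against effects as small as 12.5%. The Discussion encourages this by suggesting that a difference at 6 months could hardly be missed with CMR. If the power is far lower, that inference is unsafe.

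**Working it through.** **Inputs**
- Total 32 in two arms (Abstract; Sample size and data analysis), allocated 1:1 (Enrollment and baseline phase assessments): 16 per arm.
- Two-sided alpha 5%, target power 80%, effect 12.5%, common relative SD 48%, pilot effect 51% (all from Sample size and data analysis).

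**Attempt to reproduce the stated figure**

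Take the plain reading, with 12.5% and 48% on the same scale (per cent of the mean placebo drop).
- Standardised effect: d = 12.5/48 = 0.260.
- Power by the normal approximation: Φ(d·√(16/2) − 1.960) = Φ(0.260 × 2.828 − 1.960) = Φ(−1.22) = 0.111. The noncentral t calculation gives 0.110.
- Patients per arm for 80% power: 2 × (1.960 + 0.842)²/d² = 15.70/0.0678 = 231.5, so 232. The t test needs 233, or 466 in total.

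The stated 80% at 32 patients is not reproduced.

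**Other readings of the 48%**

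A relative SD can also mean SD divided by mean, and the text ties it to the supplemented group. The SD then depends on that group's mean drop, as a fraction of the placebo drop. Results below are from the two-sample t test.

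| Reading | SD, % of placebo drop | d | Power, 16 per arm | n per arm for 80% |
|---|---|---|---|---|
| Same scale | 48 | 0.260 | 11.0% | 233 |
| CV, supplemented mean = 0.875 of placebo | 0.48 × 87.5 = 42 | 0.298 | 12.9% | 179 |
| CV, pilot supplemented mean = 0.49 of placebo | 0.48 × 49 = 23.5 | 0.531 | 30.7% | 57 |

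**Further attempts to reach 80%**
- 32 per arm instead of 32 in total: 17.6% (SD 48) to 55.3% (SD 23.5).
- One-sided 5% test with 16 per arm: 17.8% (SD 48) to 43.0% (SD 23.5).
- Log scale with a CV of 48%: 12.7%.
- Baseline adjustment with SD 48: this multiplies the SD by √(1 − r²). Reaching 12.2 needs √(1 − r²) = 12.2/48 = 0.254, so r of about 0.97.

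**What SD would support the claim**

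With 16 per arm, the t test has 80% power at d = 1.024. For a 12.5% effect the SD would have to be 12.5/1.024 = 12.2%, about a quarter of the stated 48%.

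**What 32 patients do support**
- Same scale: detectable reduction = 1.024 × 48 = 49%.
- SD of 48% of the pilot supplemented-group mean: 1.024 × 23.5 = 24%.

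**Where the 32 may have come from**

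On the same-scale reading, the pilot's 51% gives d = 51/48 = 1.06. This needs 15 per arm by the t test (30 in total) and has 82.8% power with 16 per arm. That is close to 32 but not exact. On the CV reading with SD 23.5, the same 51% gives d = 2.17 and needs only 5 per arm, so the match disappears.

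**The case against.** The strongest reply is that the intended inputs are unknown. The 48% comes from echocardiography, CMR is more precise, and the mistake may lie in the SD quoted rather than in the 12.5%. This stands as a caution about the source of the error. It does not rescue the sentence, which prints 48% as the assumption and gives no CMR figure.

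Another reply is that 12.5 means absolute LVEF points while 48% is relative to the mean drop. An SD of 12.2 points would then imply a mean drop of 12.2/0.48, about 25 points, in the supplemented group. With a 51% reduction, the placebo drop would be 25.4/0.49, about 52 points. A patient entering at the eligibility floor of 50% would fall below zero.

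The trial is also a declared pilot that lists small size among its main limitations. That is fair, and it is why no larger sample is asked for. But the article still makes a formal power claim and tests at p < 0.05.

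A reader might infer several stronger points that the document does not support:
- **That true power is simply 11%.** This is the same-scale reading only; the wording also admits 13% to 31%.
- **That 32 patients fit only the 51% pilot effect, or that only an effect of that size is detectable.** This too depends on the same-scale reading. On the CV reading with the pilot mean, the detectable reduction is about 24%.
- **That attrition was ignored.** A condensed article may leave this to the full protocol, so its silence proves nothing.
- **That the pilot estimate can be given a confidence interval.** The Background reports eleven patients in each active group but no number for placebo, so the calculation would rest on a guess.

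**Conclusion.** The power statement is wrong as written. With 16 per arm and a two-sided 5% test, the printed effect and SD give about 11% power on the same-scale reading and about 13% to 31% if the 48% is a coefficient of variation of the supplemented-group mean. None of the two-arm variants tried reaches 80%.

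The failure to reproduce the figure is firm. The exact power and the detectable difference are conditional on what the sponsor meant by a relative SD. The pilot's 51% as the origin of the 32 is a plausible explanation on one reading, not an established fact. The calculations assume a normally distributed change, equal SDs, and all 32 patients analysed.

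**What to change.** Keep 32 patients and correct the sample size paragraph:
- State the effect and the SD actually used, on one scale, preferably absolute CMR LVEF points at 180 days. If a CMR-specific SD was used, give it and its source.
- Restate either the power for 12.5% or the difference detectable with 80% power. If the printed figures are the intended ones, that difference is a relative reduction of about 49% (same scale) or about 24% (SD of 48% of the pilot supplemented-group mean), not 12.5%. Which of the two to print depends on the inputs that the sponsor confirms.
- Add that a non-significant LVEF result is not 80%-powered evidence against a 12.5% effect.

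The cost is wording only, with no extra patients; 30 had been enrolled by 26 October 2018 (Trial status). The downside is that the stated detectable effect becomes less favourable.

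### The test and effect measure for each continuous co-primary endpoint are left to an undefined Kolmogorov-Smirnov check on the trial's own data; for skewed biomarkers, the resulting raw-scale, unadjusted comparison loses power against a pre-named log-scale analysis

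*Protocol article*

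**What the plan says.** The rule is in the protocol article under Sample size and data analysis. It has three parts:

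- The check: "Distribution will be analyzed using the Kolmogorov-Smirnov test".
- The choice of test that depends on it. A variable judged normal is compared by Student's t test. One judged non-normal is compared by Mann-Whitney instead, in the sentence that ends "correlation will be used for non-normally distributed continuous variables".
- The choice of summary, which depends on it too: "Continuous variables will be expressed as means ± standard deviation or medians and interquartile ranges depending on their distribution".

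No co-primary endpoint is exempt, and no transformation is named. The section does not say whether the check uses standard or Lilliefors critical values, at what level, or per arm or pooled. Nor does it say what happens if arms or visits disagree.

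Under Study objectives, the third co-primary endpoint is a rise in NT-ProBNP from baseline to 48 hours and/or in hs-cTnT at days 2, 4 and 90. GLS is compared at 90 and 180 days. Baseline values of both biomarkers are collected (Enrollment and baseline phase assessments).

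**The concern.** A pre-test on the outcome data means that the effect measure is not known until the data are in. hs-cTnT could be reported as a difference in means at one visit and as a rank comparison at the next. The two routes also give different answers: in simulated trials with a true biomarker effect, the t test and Mann-Whitney disagreed on significance in 12–21% of trials, so the check can settle the result.

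The second worry is efficiency. Biomarker concentrations are positive and plausibly right-skewed. Both branches of the rule, applied to raw change, ignore the log scale and make no baseline adjustment. This matters in a trial of 32 patients that lists its small size as a main limitation, and whose own earlier pilot (Background) reported an NT-ProBNP signal for the DHA formula.

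**Working it through.** **1. Arm size.** The article says "a sample size of 32 will be required to provide 80% statistical power to detect a 12.5% ΔLVEF reduction assessed by CMR". With 1:1 allocation that is 16 per arm. The figure 32 cannot be reproduced from the stated inputs. With n per arm = 2(1.960 + 0.842)²(SD/Δ)², SD 48 and Δ 12.5 give 15.7 × 14.75 ≈ 232 per arm, or 464 in total; Δ 51 gives 15.7 × 0.886 ≈ 14 per arm, or 28 in total. That is a separate matter. Only the arm size is used here, and the article gives no figure for the performance of the normality check.

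**2. How often the check detects skew.** Simulated lognormal data with estimated mean and SD, tested at 5%. The critical value at n = 16 is 0.327 (classic) or 0.213 (Lilliefors).

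| log-SD (assumed) | Classic, one arm of 16 | Lilliefors, one arm of 16 | Classic, pooled 32 |
|---|---|---|---|
| 0.5 | 0.8% | 28% | 4% |
| 0.8 | 5% | 54% | 26% |
| 1.0 | 12% | 68% | 48% |
| 1.5 | 34% | 90% | 87% |

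The answer depends heavily on details that the protocol does not give.

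**3. Power for the biomarkers.** Assumptions: lognormal values, log-SD 0.6–1.0, baseline correlation 0.5–0.7, effect 0.7 log-SD, raw change from baseline, 16 per arm, check applied in each arm.

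| Procedure | Trials sent to the t test | Power |
|---|---|---|
| The rule, classic test | 78–98% | 35–62% |
| The rule, Lilliefors | 15–59% | 41–64% |
| ANCOVA on logs, adjusted for log baseline | none | 58–77% |

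The last row can be checked by hand. In log-SD units the residual SD is √(1 − ρ²), and the non-centrality is 0.7/√(1 − ρ²) × √(16/2).

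- ρ = 0.5: 0.7/0.866 × 2.828 = 2.29. Power ≈ Φ(2.29 − 2.045) ≈ 60%.
- ρ = 0.7: 0.7/0.714 × 2.828 = 2.77. Power ≈ Φ(2.77 − 2.045) ≈ 77%.

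**4. Where the gap comes from.** A perfect check would send every skewed sample to Mann-Whitney. Against Mann-Whitney used throughout, the classic rule loses only about 1–8 points. A wider set of runs, with and without a common post-chemotherapy rise in both arms, gave 26–65% for the classic rule, 31–68% for Mann-Whitney throughout and 58–76% for log-scale ANCOVA; there the check cost 1–9 points. The remainder is due to scale and baseline adjustment.

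The adjustment part can be isolated. An unadjusted t test on log ratios has SD √(2(1 − ρ)).

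- ρ = 0.5: 0.7/1.000 × 2.828 = 1.98. Power ≈ Φ(1.98 − 2.042) ≈ 48%.
- ρ = 0.7: 0.7/0.775 × 2.828 = 2.56. Power ≈ Φ(2.56 − 2.042) ≈ 70%.

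Baseline adjustment on the log scale is therefore worth roughly 12 and 7 points (60 − 48 and 77 − 70).

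**5. Type I error and normal data.** Across all null scenarios in the re-calculation, covering lognormal levels and change scores, the two-step rule rejected in 4.2–5.6% of trials. For normal data with a 1-SD effect, the rule and a plain t test both have 78% power.

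**The case against.** The best defence has four parts.

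- **The check may not be weak.** A reader might infer that it has almost no power at 16 per arm, so that skewed biomarkers will usually be passed as normal. That holds only for uncorrected critical values applied per arm at moderate skew. The protocol does not say that this version will be used, and with Lilliefors values most samples at log-SD 0.8 or above go to Mann-Whitney. This objection stands.
- **The loss is mostly not due to the check.** It also limits itself: where the raw t test is worst, the check rejects more often. This stands too. A reader should not attribute the whole gap to the Kolmogorov-Smirnov test.
- **The harm is narrow.** A reader might infer inflated false positives, or damage to all four co-primary endpoints. Neither is shown. The sample size rests on "Assuming normal distribution and a common relative standard deviation of 48% (supplemented group", and the Discussion aligns the trial with others that compare mean differences, so LVEF would probably be analysed as a mean difference in any case.
- **The inputs are hypothetical, and transformations belong in an analysis plan.** The article gives no biomarker spread, shape or correlation, and does not say whether the rise is absolute or relative. The figures are therefore conditional. But the article does not stay silent and defer the choice: it fixes a rule, and that rule is what is criticised. The power gain over the rule remains about 11–19 points even under the Lilliefors version.

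Baseline adjustment for LVEF, GLS and QTc is good practice and does not follow from the flaw in the check.

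**Conclusion.** The point holds in a limited form. The protocol makes the test and the summary measure for every continuous co-primary endpoint depend on an under-specified check of the trial's own data, so the reported measure can change between endpoints and visits. That much follows from the text alone.

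The efficiency loss is conditional. It concerns the biomarker co-primary endpoint, and it assumes right-skewed values analysed as raw change. Under the assumptions in step 3, power is lower than with a log-scale, baseline-adjusted analysis whichever version of the check is used. The check itself is the minor cause. The validity of the tests is not in question. The change is worth making because it is nearly free, but the flaw is not fatal to the trial.

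**What to change.** Delete the Kolmogorov-Smirnov step and name one method per co-primary endpoint before unblinding:

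- **NT-ProBNP and hs-cTnT:** ANCOVA on log values at each named visit, adjusted for log baseline, reported as a geometric-mean ratio with its confidence interval. State how results below the assay limit enter the log.
- **LVEF, GLS and QTc:** a baseline-adjusted difference in means with its confidence interval.
- **Mann-Whitney:** only as a named sensitivity analysis that does not replace the primary result.

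The choice between mean and median for descriptive tables can also be fixed by variable.

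The cost is wording only. The baseline values are already collected, and no patients or visits are added. One consequence should be accepted openly: the biomarker effect is then read as a ratio between arms instead of an absolute change. The article reports 30 patients enrolled by October 2018, so the change should be dated and documented as made before any unblinded data were seen.
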